## Abstract

**Background:**

Suboptimal vitamin D status is highly prevalent in Northern communities, particularly in those patients with chronic diseases such as diabetes and chronic renal disease. Emerging literature suggests that adherence to daily vitamin D supplementation may be an important factor influencing vitamin D status and overall bone health, but compliance with therapies for bone health is a major challenge. It is unknown what level of vitamin D supplementation will ameliorate or improve suboptimal vitamin D status in patients with diabetic nephropathy or contribute to improved bone health, particularly for those living in northern climates.

**Methods/Design:**

The study purpose was to examine two different strategies of vitamin D3 supplementation; daily dosing of 2000 IU per day verses monthly dosing of 40,000 IU per month on markers of vitamin D status, bone health and to examine whether adherence, quality of life and patient satisfaction with the supplementation strategy differs between the two vitamin D strategies in adults diagnosed with diabetic nephropathy.

**Discussion:**

The need for RCTs assessing higher doses of vitamin D_3_ supplementation at varying frequencies of administration and its impact on bone health in adults with diabetes and chronic kidney disease are needed.

**Trial registration:**

ClinicalTrials.gov NCT01476501.

## Background

Suboptimal vitamin D status (25(OH)D <75 nmol/L) is associated with the development and progression of both diabetes and chronic kidney disease (CKD) [1]. Within the general North American population 16-52% have suboptimal vitamin D status; the prevalence of vitamin D insufficiency increases to 86% in the diabetic population and those with concurrent kidney disease are 1.78-fold more likely to be vitamin D deficient [2-4]. Patients living in northern communities are at particular risk for vitamin D insufficiency due to limited sunlight exposure, further increasing their risk for low bone mineral density (BMD) and fragility fractures [3,5-10]. Recent evidence indicates that up to 40-90% of patients with stage 3–4 CKD have insufficient/deficient vitamin D status [2,5,11,12]. By the time CKD patients reach dialysis, approximately 75% have metabolic bone disease [13].

Unlike other nutrients, recommendations for vitamin D are not based on food sources as there are very few dietary options available (e.g. fish, liver and fortified dairy products), but rather are designed to compensate for a deficiency of sunlight [14]. This places the individual living in northern climates at particular risk for inadequate vitamin D status, especially in the winter months when sunlight exposure is unlikely to contribute to overall vitamin D status. Most evidence suggests that when vitamin D requirements are met, it is with a combination of dietary vitamin D and a supplement [15-22]. Patients with diabetic nephropathy are at increased risk for poor dietary intake of vitamin D due to restrictions on vitamin D rich foods/beverages (e.g. dairy based products) as these products also have a high carbohydrate, phosphorus and/or potassium content. It is unknown what level of vitamin D supplementation will ameliorate or improve suboptimal vitamin D status in patients with diabetic nephropathy or contribute to improved bone health, particularly for those living in northern climates [5,7,10]. A recent study in patients with stage 3–4 CKD demonstrated that daily oral supplementation of vitamin D_3_ (1,000 IU/d) for three months resulted in a mean increase in serum 25(OH)D of 25 nmol/L (40 ± 15 nmol/L pre- vs. 68 ± 25 nmol/L post-supplementation); a significantly lower level of 25(OH)D than is thought to optimize bone health (>100 nmol/L) [12,23-25].

Emerging literature suggests that adherence to daily vitamin D supplementation may be an important factor influencing vitamin D status, and compliance with therapies for bone health (like other asymptomatic conditions) is a major challenge [26-28]. Chronic diseases, such as poor bone health, as well as suboptimal vitamin D status, have been associated with reduced quality of life (QoL) [26,29-31]. Despite the potential for improved functional ability and independence, only 50-69% of individuals prescribed osteoporosis medications (e.g. bisphosphonates, vitamin D and calcium) comply to them regularly (e.g. consume 80% of the time), and only 25-35% are compliant for more than one year [29-31]. This suggests that current modes of vitamin D supplementation in adults with diabetic nephropathy, particularly low dose daily administration (<1,000 IU/d), may be ineffective at optimizing vitamin D status. Higher daily doses (>1,000 IU/d) or the use of high dose, less frequent modes of administration (monthly vs. daily), need to be explored to ensure improved compliance to dosing strategies and adequacy of overall vitamin D status, particularly in those populations at high risk for vitamin D insufficiency and suboptimal bone health (e.g. diabetic nephropathy).

## Purpose

The first study aim was to investigate the impact of daily vs. monthly vitamin D_3_ supplementation on vitamin D status and markers of bone health in adults with diabetic nephropathy. The second study aim was to compare participant adherence and satisfaction between two different vitamin D_3_ supplementation strategies (daily vs. monthly), and quality of life (QoL).

### Objectives

1. Examine the impact of two approaches to high dose, oral, vitamin D_3_ supplementation (2,000 IU/d vs. 40,000 IU/m) for 6 months on overall vitamin D status (25(OH)D and 1,25(OH)_2_D) and markers of bone turnover (bone-specific alkaline phosphatase, osteocalcin, N-telopeptide of type 1 collagen) in adult patients with diabetic nephropathy.

2. Examine daily vs. monthly vitamin D_3_ supplementation strategies in regards to adherence, patient satisfaction and quality of life in adult patients with diabetic nephropathy.

### Hypotheses

1. Vitamin D_3_ supplementation (2,000 IU/d vs. 40,000 IU/m) for 6 months will result in significantly improved overall vitamin D status and improved markers of bone health in adult patients with diabetic nephropathy. Serum 25(OH)D will increase by a minimum of 25–50 nmol/L post-supplementation. Markers of bone resorption will decrease and markers of bone formation will increase after 6 months of vitamin D_3_ supplementation when compared to baseline levels.

2. Monthly dosing of vitamin D_3_ (40,000 IU/m) over 6 months will result in improved patient adherence and satisfaction with vitamin D_3_ supplementation when compared to daily dosing of vitamin D_3_ (2,000 IU/d) resulting in improved overall vitamin D status, bone health parameters, and quality of life.

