### Inclusion criteria

1) Adult (18–80 years) patients diagnosed with diabetes (Type 1 and Type 2) and stage 1–4 CKD (Glomerular Filtration Rate (GFR) 15–89 mL/min/1.73 m^2^) [34].

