### Laboratory investigations

To avoid risk of hypoglycemic events due to variations in appointment availability (e.g. insulin regimen incompatibility with fasting and later appointment times), random serum/plasma samples for measurement of routine clinical blood work and study blood work were collected. However, most blood samples were collected between 10 am-2 pm; approximately 2 hours post meal consumption (of either breakfast or lunch) to minimize the potential influences of variable blood collection times on bone turnover marker expression [39].

Blood samples were collected onsite at each research visit by a trained phlebotomist using validated techniques and tubes (SST gel for serum, and lithium heparin PST gel and EDTA plasma). Once collected, blood samples were immediately held at 2-8°C until processing by the research team or provincial laboratory system. Patients routinely receive clinical blood work to assess their glycemic control, kidney function and overall health, including: estimated GFR (eGFR), fasting/random blood glucose (FBG/RBG), urea, creatinine, hemoglobin A1c (HbA1c), calcium, albumin, phosphorus, magnesium, 25(OH)D and PTH. These variables were collected at all 3 study visits (except PTH) along with 1,25(OH)_2_D status. Serum PTH, bone turnover markers and fibroblast growth factor-23 (FGF-23) were collected at baseline and 6 month follow-up study visits.

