Routine clinical blood work, 1,25(OH)_2_D and PTH were measured by validated, specific and sensitive methodologies used by the provincial laboratory system. Estimated GFR was calculated using a validated online equation provided by K/DOQI (Modification of Diet in Renal Disease (MDRD) study group and the Chronic Kidney Disease Epidemiology Collaboration (CKD-EPI) group; http://www.kidney.org/professionals/kdoqi/gfr_calculator.cfm). Bone turnover markers were analyzed by the research team using standardized commercial ELISA kits. After blood collection, EDTA plasma and serum clot samples (e.g. SST gel) were kept for approximately 30–60 minutes at 2-8°C and then centrifuged at 2,500 RPM at 4°C for 10 minutes (CR4.22 centrifuge, Jouan, Winchester, VA, USA). Recovered serum and plasma were aliquoted into clean micro-tubes according to volumes required for each specific assay to be tested in duplicate. Samples were stored frozen at −80°C until ELISA testing, and prepared according to the manufacturer instructions for each commercial ELISA kit: serum intact osteocalcin (OC; MicroVue Osteocalcin EIA Kit, Quidel, San Diego, CA, USA), serum bone-specific alkaline phosphatase (BAP; MicroVue BAP EIA Kit, Quidel, San Diego, CA, USA), serum N-telopeptide of type 1 collagen (NTx; Osteomark NTx Serum, Wampole Laboratories, Princeton, NJ, USA), and plasma intact fibroblast growth factor-23 (FGF-23; Human Intact FGF-23 ELISA Kit, Immunotopics Inc, San Clemente, CA, USA). The intra-assay (a) and inter-assay (b) coefficient of variance (CV) for these commercial kits are as follows: OC a) 4.8-10.0%, b) 4.8-9.8%; BAP a) 3.9-5.8%, b) 5.0-7.6%; NTx a) 4.6-13.99%, b) 6.9-13.99%; and FGF-23 a) 2.6-4.4%, b) 6.1-6.5%.

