### Bone health

Bone health was assessed by measurement of BMD and plasma/serum levels of bone turnover markers. BMD was measured using DXA (non-invasive gold standard) to characterize bone health of participants at time of study entry. Bone turnover markers were measured at baseline and at 6 months; bone resorption: N-telopeptide type 1 collagen (NTx); and bone formation: bone-specific alkaline phosphatase (BAP) and osteocalcin (OC) [34]. Serum PTH and fibroblast growth factor-23 (FGF-23; measure of bone-kidney axis) were measured at baseline and 6 months to assess how serum PTH/FGF-23 concentrations change with our vitamin D supplementation strategies.

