Continuous and categorical variables (e.g. 25(OH)D, lab parameters, BMD T-scores, adherence scores) were quantitatively analyzed, and open-ended questions regarding participants’ perceived facilitators and barriers were categorized into key themes. Bivariate and univariate analysis were done to assess the potential effect of these variables on vitamin D status and bone health (bone turnover markers).Variables shown to be associated with a poor vitamin D status were assessed using multivariate logistic regression models to determine risk for development of vitamin D deficiency and poor bone health. Regression analysis was also conducted to assess correlation between biochemical parameters (PTH, 25(OH)D, 1,25(OH)_2_D, calcium, phosphorus, magnesium, albumin, eGFR, RBG) and bone turnover markers. Analysis of variance was performed to assess for significant differences in vitamin D status and bone turnover markers over the intervention period in both groups. Regression analysis was performed with serum 25(OH)D and plasma PTH as categorical variables; e.g. 25(OH)D sorted by greater/less than 75 nmol/L and plasma PTH sorted by greater/less than 7.15 pmol/L, the optimal concentrations for bone health [5,26]. Where necessary, vitamin D was adjusted for potential confounding variables (e.g. age, gender, ethnicity, disease severity) using an analysis of co-variance. When adherence to daily vitamin D dosing regimen was greater or less than 69%, the variation in compliance was also accounted for in an analysis of co-variance. For variables demonstrating skewed distributions a logarithmic transformation was used to normalize the data.

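### Hypothesis 1 reads uncontrolled bone-marker change as a supplement effect, but the change test has no kidney-function term and the arm comparison makes no use of baseline values as covariates

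*Protocol article*

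**What the plan says.** - **Hypotheses, no. 1:** "Markers of bone resorption will decrease and markers of bone formation will increase after 6 months", judged against baseline. Under Study design both arms receive vitamin D3, daily or monthly, so there is no untreated arm.
- **Bone health:** BAP, osteocalcin (OC) and NTx are measured at baseline and 6 months only. PTH and FGF-23 follow the same schedule, "to assess how serum PTH/FGF-23 concentrations change with our vitamin D supplementation strategies".
- **Inclusion criteria:** patients have diabetes and CKD with "Glomerular Filtration Rate (GFR) 15–89 mL/min/1.73 m^2".
- **Laboratory investigations:** eGFR is in the routine panel, of which the article says "These variables were collected at all 3 study visits (except PTH"). It also says "Estimated GFR was calculated using a validated online equation provided by K/DOQI" and names two equation groups, MDRD and CKD-EPI.
- **Statistical analysis, test of change:** "Analysis of variance was performed to assess for significant differences in vitamin D status and bone turnover markers over the intervention period in both groups". The dosing arms are compared by repeated measures ANOVA, followed by Bonferroni-corrected pair-wise t-tests within and between groups. No kidney-function term is named for either.
- **Statistical analysis, adjustment:** "Where necessary, vitamin D was adjusted for potential confounding variables (e.g. age, gender, ethnicity, disease severity) using an analysis of co-variance". Bone markers are not mentioned in that sentence.
- **Statistical analysis, kidney function elsewhere:** severity of kidney disease is a listed candidate factor and is examined against bone turnover markers in bivariate and univariate analyses. A separate regression relates eGFR, among other parameters, to the markers.

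**The concern.** Two separate things are at stake.

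1. **The within-arm claim.** Hypothesis 1 attributes a before-after change to the supplement. With no untreated arm, anything else that moves the markers over 6 months is included in that change. In a CKD population a drift in kidney function is an obvious candidate, and the article itself treats severity of kidney disease as a possible factor in bone health. If a marker's serum level depends on GFR, a mean fall in eGFR shifts the mean marker change at constant bone turnover. The shift could look like a gain or hide one, depending on the marker and the direction of the dependence.

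2. **The between-arm claim.** Drift should be similar in randomised arms, so the issue here is precision, not bias. Baseline markers and baseline eGFR are already collected, yet the named method does not use them as covariates.

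**Working it through.** **No stated figure to reproduce.** The sample size of 120 is based on 25(OH)D. The article gives no marker SD, no expected eGFR decline and no relation between marker and GFR.

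**Step 1. Does any stated analysis correct the change test?**

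| Analysis in the article | Outcome | Kidney term | Corrects the mean marker change? |
|---|---|---|---|
| ANOVA over time; repeated measures ANOVA with Bonferroni t-tests | Bone markers, vitamin D | None named | No |
| ANCOVA, where necessary | Vitamin D | Disease severity | Not stated for markers |
| Bivariate and univariate analyses | Bone markers, vitamin D | Severity of kidney disease | No: a separate association |
| Regression on biochemical parameters | Bone markers | eGFR | No: a separate association |

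An association estimated alongside the test leaves the tested mean change as it was.

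**Step 2. How a drift would enter (illustration; every input is assumed).** Take the marker as proportional to GFR^-b, with constant bone turnover. For a fall of d from starting value G:

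rise = (G/(G - d))^b - 1

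| G | d | b | Calculation | Marker rise |
|---|---|---|---|---|
| any | 0 | any | 1 - 1 | 0% |
| 50 | 1 | 0.3 | (50/49)^0.3 - 1 | 0.6% |
| 50 | 1 | 0.5 | (50/49)^0.5 - 1 | 1.0% |
| 50 | 2 | 0.5 | (50/48)^0.5 - 1 | 2.1% |
| 30 | 3 | 0.5 | (30/27)^0.5 - 1 | 5.4% |
| 30 | 5 | 1 | (30/25)^1 - 1 | 20% |

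The result runs from nothing to large, so the documents cannot settle the size. A stable mean eGFR gives no mean bias in this sense. The wide GFR range at entry does not bias a within-patient change; it only means that the same absolute fall is a larger relative fall at low GFR.

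These shifts are not turned into false-positive rates. The article applies Bonferroni corrections without giving the number of comparisons, so a rate at an uncorrected 5% level would not describe the stated test. The correction makes a false significant result less frequent but leaves the shift in the mean.

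**Step 3. Precision of the arm comparison.** With two time points, the group-by-time term of a repeated measures ANOVA is a comparison of change scores. Let the SD be equal at both visits (s) and let r be the correlation between them (both assumed), with n per arm.

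- Variance of the difference in change: (2/n) × 2s²(1 - r)
- Variance of the ANCOVA difference: (2/n) × s²(1 - r²)
- Ratio: (1 - r²)/(2(1 - r)) = (1 + r)/2

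Completers per arm are 60 × 0.85 = 51, using the article's 15% attrition allowance.

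| r (assumed) | Variance ratio | 51 completers with ANCOVA match, on change scores |
|---|---|---|
| 0.3 | 0.65 | 51/0.65 = 78 |
| 0.5 | 0.75 | 51/0.75 = 68 |
| 0.7 | 0.85 | 51/0.85 = 60 |
| 0.9 | 0.95 | 51/0.95 = 54 |

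The cost is two residual degrees of freedom: 102 - 2 = 100 becomes 98 with baseline marker and baseline eGFR in the model.

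**The case against.** The strongest case against has five parts.

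- **The mechanism is not in the documents.** Nowhere does the article say that OC or NTx rises as GFR falls. This stands. A reader might infer that falling GFR will produce a false formation gain or mask a fall in resorption; the documents do not support that. For the same reason they give no ground for ranking BAP above OC as the formation marker.
- **Kidney function is not ignored.** A reader might infer that the plan takes no account of it for bone markers. That is wrong: eGFR and severity of kidney disease are both related to the markers. The gap is confined to the change test.
- **An article condenses.** Covariate lists are often left to a fuller document. This carries some weight, but the article does name an adjustment and attaches it to vitamin D, and it names the marker test without one. The point rests on what is stated.
- **Drift alone would not mimic the whole hypothesis.** If OC and NTx both rose, the resorption half of Hypothesis 1 would be contradicted. This stands for the joint pattern, but each half can still be misread alone, and the article does not tie them together.
- **An eGFR covariate does not create a control group.** This stands. Other time trends remain, and eGFR change is measured after randomisation and may respond to treatment. Hence the adjusted change can only be supportive.

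**Conclusion.** The point holds in a limited form. As written, the test of Hypothesis 1 on bone markers cannot separate a supplement effect from a mean drift in eGFR, and the separate eGFR analyses do not repair that. Whether bias arises depends on two things that the documents do not give: a dependence of the markers on kidney function, and a mean change in eGFR over 6 months. Its size cannot be fixed: it is zero with stable eGFR and about 0.6% to 20% in the assumed cases with a fall.

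A reader might infer that the daily-versus-monthly comparison is biased too. It is largely protected by randomisation. What it loses is precision: ANCOVA has 0.65 to 0.95 of the change-score variance for assumed correlations of 0.3 to 0.9, given equal variances at the two visits.

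This is an inexpensive improvement to analysis and interpretation, not a flaw that invalidates the trial.

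**What to change.** In the Statistical analysis section:

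1. **Arm comparison.** Compare 6-month OC, BAP, NTx, PTH and FGF-23 between arms by ANCOVA with the baseline value of the same marker and baseline eGFR as covariates, log-transformed where skewed, as the article already provides.
2. **Within-arm change.** Beside the raw change, report as a supportive sensitivity analysis the change adjusted for the same patient's eGFR change. Evaluate it at zero eGFR change, because centring the covariate at its mean would only return the raw mean. Use one eGFR equation at both visits.
3. **Interpretation.** State that change from baseline without an untreated arm is not by itself evidence of a bone effect. Apply this to PTH and FGF-23 as well.

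**Cost:** wording and one or two degrees of freedom; no new data, since eGFR is taken at every visit. Because eGFR change is post-randomisation, item 2 must not be used for the randomised contrast. Item 2 addresses only eGFR drift, and other time trends remain.

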## Methods

### Study design

The study design was a randomized, controlled, open-label trial comparing the effectiveness of two vitamin D_3_ dosing strategies (monthly vs. daily) on vitamin D status and markers of bone health in adults with diabetes and nephropathy over a 6 month period. Patients were randomized to one of the two vitamin D_3_ supplementation strategies in blocks of 30 using a random number generator (http://www.randomizer.org) by one graduate student (SJ): once monthly (40,000 IU/m; n = 60) or once daily (2,000 IU/d; n = 60) for six months. All members of the research team (with the exception the graduate students (SJ/MH)) were blinded to study allocation. Both vitamin D supplements contain vitamin D_3_ (cholecalciferol) in gel capsule form; Jamieson Natural Sources® Vitamin D 1,000 IU Soft gel (NPN 80017530), and EURO-Pharm International Canada Inc.® EURO D 10,000 IU (DIN 02253178). The two dosing regimens were: 2 capsules of 1,000 IU vitamin D daily (total dose = 2,000 IU/d), or 4 capsules of 10,000 IU vitamin D at the end of each month (total dose = 40,000 IU/m). The daily dose was selected based on results from findings that showed that patients with diabetes with stage 3–4 CKD in Northern Alberta where supplementation with 1000 IU/D vitamin D3 resulted in serum increases of 25(OH) vitamin D less than 25 mmol/L [5,7]. A monthly dose of 40,000 IU/m vitamin D_3_ was chosen to achieve equivalent supplementation to daily dosing assuming an adherence rate of 69%, and with the goal of obtaining a serum 25(OH)D concentration of 100 nmol/L [27,32].

This study was approved by the Human Research Ethics Board at the University of Alberta (File Number: Pro00022639), has received a “No Objection Letter” from Health Canada (Control File Number 148625), and is a registered clinical trial (NCT01476501). The study was monitored by a Drug and Safety Monitoring Board (DSMB) with annual safety reports submitted as per Health Canada protocol. Reporting of study results will be according to the CONSORT (Consolidated Standards of Reporting Trials) Guidelines [33].

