### Participants

Patients were recruited from Northern Alberta Renal Program (NARP) clinics at Alberta Health Services (AHS) in Edmonton, Alberta between November 2011 and December 2013. This is a multidisciplinary program (endocrinologists, nephrologists, registered nurses (RN), registered dietitians (RD), pharmacists and social workers) that provides care to over 1,500 patients with diabetic nephropathy in northern Alberta. Sixty adults with diabetes and nephropathy per vitamin D_3_ supplementation group were recruited into this study (n = 120 total). Potential participants were approached by a member of the clinical team (e.g. RD or RN) and asked if a research team member could discuss this study with them. If verbal consent was provided, then a research team member contacted the patient, explained the study to them and determined their eligibility for participation in this RCT; if eligible and agreed by the patient, informed consent was signed and the baseline study appointment was booked. Subsequent study visits (e.g. 3 month and 6 month follow-up appointments) were booked via telephone calls made approximately 2 months later to follow-up with the participants and address any questions or concerns they may have had about their supplement strategy. Patient eligibility for this RCT was determined upon information available in the medical chart at time of screening. Inclusion/exclusion criteria are as follows:

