### Statistical analysis

Data analysis was performed on an intention-to treat basis as well as a per-protocol basis. Analyses were performed using Microsoft Excel 2010 and Statistical Analysis Software (SAS; version 9.3 SAS Institute, Cary, NC, USA). Statistical significance was determined at p < 0.05. Continuous variables were expressed as mean, median, ranges, and standard error (SE) or standard deviation (SD). The differences between dosing type (daily vs. monthly) over the intervention period were assessed by repeated measures analysis of variance, followed by a post-hoc pair-wise t-test with Bonferroni corrections to assess for within and between group comparisons. Potential risk factors for the development of vitamin D insufficiency (serum 25(OH)D <75 nmol/L) and poor bone health (T-scores < −2 SD) in adults with diabetic nephropathy include bone turnover, vitamin D intake, vitamin D status (serum levels of 25(OH)D and 1,25(OH)_2_D), age, gender, ethnicity, severity of kidney disease, diabetic management/control, exposure to sunlight, level of activity, and psychosocial and lifestyle factors.

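### The blocks of 30 are probably half-year calendar strata, and the stated between-arm model has no block or season term, so the interval for 25(OH)D is likely to be somewhat too wide if season matters

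*Protocol article*

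**What the plan says.** Study design allocates patients "in blocks of 30 using a random number generator" to "once monthly (40,000 IU/m; n = 60) or once daily (2,000 IU/d; n = 60) for six months". Participants gives recruitment "in Edmonton, Alberta between November 2011 and December 2013".

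Statistical analysis states the between-arm method: "The differences between dosing type (daily vs. monthly) over the intervention period were assessed by repeated measures analysis of variance". Bonferroni-corrected t-tests come next, for contrasts inside each arm and across arms. On covariates the same section says: "Where necessary, vitamin D was adjusted for potential confounding variables (e.g. age, gender, ethnicity, disease severity) using an analysis of co-variance". Block and season are not among the covariates given as examples.

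Two other places treat the primary outcome as seasonal. The section on the sunlight questionnaire says the instrument is there to help allow for seasonal variation. The Discussion says that enrolling over two calendar years deals with it.

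**The concern.** Blocking forces the arms to be balanced over stretches of recruitment. Whatever moves the outcome between those stretches is then balanced between arms by design. A model that omits the blocks still counts that movement as residual noise, so its standard error for the arm difference is larger than the design warrants.

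Blocks are usually small and the loss is trivial. Here each block probably spans about half a year, in a trial whose main outcome depends on sunlight. Spreading enrolment over two years, which the Discussion relies on, balances season between arms but does not take seasonal variance out of the error term; a model term does. At stake is some precision and power in the randomised comparison of daily with monthly dosing.

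**Working it through.** **Blocks.** 120 / 30 = 4 blocks. November 2011 to December 2013 is 26 calendar months inclusive; 26 / 4 = 6.5 months per block (25 / 4 = 6.25 if counted month to month). This assumes even accrual. A 15:15 split within blocks is inferred from two arms of 60 and is not stated.

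**General relation.** If block explains a share f of outcome variance, the ratio of the standard error (SE) without block to that with block is about 1/√(1 − f): 1.005 at f = 1%, 1.026 at 5%, 1.054 at 10%, 1.118 at 20%. The article gives no f, so it has to come from an assumed seasonal swing.

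**A fixed shift between blocks.** A shift that is the same at every visit cancels from change over time. In one simulated data set with a 20 nmol/L shift between alternating blocks, the SE of the arm difference in change was 3.743 without block and 3.740 with it. At the 6-month visit alone it was 3.985 and 3.61.

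**A seasonal swing.** Season does not cancel. Baseline and 6 months are half a yearly cycle apart, so a swing of ±A enters the change as A·cos(θ + π) − A·cos θ = −2A·cos θ, that is, ±2A.

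**SD of change.** The only SDs in the article are 15 before and 25 after supplementation, from a cited study in the Background. With an assumed correlation of 0.5: √(15² + 25² − 2·0.5·15·25) = √475 = 21.8 nmol/L. With 15% loss, 51 per arm remain, and the SE with no calendar effect is 21.8·√(2/51) = 4.32.

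**Expected SE without block.** Averaged over a yearly cycle the swing adds variance (2A)²/2 = 2A². For A = 5: √((475 + 50)·2/51) = 4.54. For A = 12.5: √((475 + 312.5)·2/51) = 5.56.

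**Simulation.** Four 15:15 blocks, uniform accrual over 26 months from November, 15% random loss, 4,000 trials per setting. SE of the arm difference in 6-month change:

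| Swing (nmol/L) | Seasonal phase | Without block | With block | Excess |
|---|---|---|---|---|
| 0 | – | 4.31 | 4.32 | −0.2% to −0.3% |
| ±5 | random | 4.55 | 4.48 | 1.4% |
| ±5 | September peak | 4.52 | 4.42 | 2.3% |
| ±12.5 | random | 5.55 | 5.19 | 7.1% |
| ±12.5 | September peak | 5.49 | 4.89 | 12.2% |

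At ±12.5 the type I error without block was 3.9% (random phase) and 3.2% (September peak). With block it was 5.2% and 4.8%.

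For the 6-month value alone (SD 25), the excess averaged over phase was 0.1% at ±5 and 1.7% at ±12.5. With a September peak it was 0.3% and 2.7%.

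**In patients.** An excess of 1.4% to 7.1% in SE equals losing 1 − 1/1.014² = 2.7% to 1 − 1/1.071² = 12.8% of the information, about 3 to 13 of 102 completers.

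**The case against.** The strongest objection is that this is a condensed article. The exact factors in a repeated-measures model are often left to the full protocol or analysis plan, and the covariate list is explicitly open-ended. That stands: the missing term shows no error, and nothing in the article contradicts itself here. The point is a suggestion about the model as stated.

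Second, the size depends on between-block variance, within-block balance and even accrual, none of which is reported. That also stands. A September peak suits a northern site, but without the actual accrual the position of the blocks against the seasons is unknown, so the phase-averaged figures are the fairer summary.

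Third, block is a blunt proxy for season. At ±12.5 nmol/L it recovers (5.55² − 5.19²)/(5.55² − 4.31²) = 32% of the calendar variance averaged over phase, and (5.49² − 4.89²)/(5.49² − 4.31²) = 54% with a September peak. The trial also collects sunlight exposure for each patient, which might absorb more. However, the article does not place sunlight in the between-arm model. Block has the advantage of being fixed by the allocation.

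A reader might infer that the interval is certainly too wide, or that the comparison is biased or invalid. The documents support neither. With no calendar effect the excess vanishes. With one, the test errs on the cautious side. Nor does the point bear on the sample size, which rests on change from baseline within each group. Extending it to bone turnover markers would also go too far, because the article attributes seasonal variation to vitamin D status only.

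**Conclusion.** The point holds as a minor, conditional gain in efficiency. If season shifts 25(OH)D, as the article indicates, the stated between-arm analysis is likely to give an interval slightly wider than the design warrants. The size is about 1-7% in SE for the 6-month change, averaged over seasonal phase, for swings of ±5 to ±12.5 nmol/L. It can reach about 12% where the blocks line up well with the seasons. For a single visit it is under 2% averaged over phase. These figures assume 15:15 blocks, even accrual, an SD of change of 21.8 nmol/L and a yearly sinusoidal swing. The direction is conservative, and no conclusion is invalidated.

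**What to change.** Add randomisation block (four levels) and block-by-time to the between-arm repeated-measures model for 25(OH)D. Block alone is not enough there, because only its interaction with time reaches the change contrast. Equivalently, put block in a model for the 6-month change. Report this as the main between-arm result. Use for bone markers is optional.

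Block is known from the allocation list, so no new data are needed. The cost is 3 degrees of freedom in the change model and a few more for block-by-time, about 0.2% in SE if calendar time has no effect.
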